# The effects of intermittent fasting diet alone or in combination with probiotic supplementation in comparison with calorie-restricted diet on metabolic and hormonal profile in patients with polycystic ovary syndrome: study protocol for a randomized clinical trial

**DOI:** 10.1186/s13063-023-07691-5

**Published:** 2023-10-25

**Keywords:** Intermittent fasting, Probiotics, Polycystic ovary syndrome

## Abstract

**Introduction:**

Polycystic ovary syndrome (PCOS) is one of the most common endocrine disorders in females characterized by ovulatory dysfunction, hyperandrogenism, and other metabolic disorders. Both intermittent fasting and specific probiotics have been suggested to help improve patients with PCOS through changes in gut microbial composition, circadian clock, and metabolic regulation. Therefore, the present study aims to investigate the effects of intermittent fasting alone or in combination with probiotic supplementation compared to the calorie-restricted (CR) diet on anthropometric measures, metabolic status, inflammation, and oxidative stress in women with PCOS.

**Methods:**

We will carry out a randomized clinical trial for 8 weeks. Participants will be randomly assigned (1:1:1) to one of the three groups: (1) a 14:10 early time-restricted feeding (TRF) diet with probiotic supplementation (*n* = 30); (2) a 14:10 early TRF diet with placebo supplementation (*n* = 30); (3) a CR diet (energy-restricted 25% of required calories) with placebo supplementation as a control group (*n* = 30). The primary outcomes will be changes in body weight and insulin resistance. However, glycemic control, lipid profile, metabolic parameters, sex hormone-binding globulin, dehydroepiandrosterone, anti-Mullerian hormone, free androgen index, hirsutism, acne, antioxidant and oxidant status, inflammation, anthropometric measures, mental health, sleep quality, appetite, eating behavior, food craving, and blood pressure are secondary outcomes. All outcomes of this study will be evaluated in pre- and post-intervention.

**Discussion:**

We hypothesized that 10-h TRE administered alone or in combination with probiotic supplementation to overweight and obese PCOS subjects would lead to weight loss and improved metabolic, hormonal, inflammatory, and antioxidant markers compared to control subjects following a standard 3-meal-per-day CR diet.

**Ethical aspects:**

The current trial received approval from the Medical Ethics Committee of Tehran University of Medical Sciences, Tehran, Iran (IR.TUMS.MEDICNE.REC.1401.425).

**Trial registration:**

Iranian Registry of Clinical Trials IRCT20121110011421N5. Registered on 3 October 2022.

**Supplementary Information:**

The online version contains supplementary material available at 10.1186/s13063-023-07691-5.

## Introduction

Polycystic ovary syndrome (PCOS), one of the most common endocrine disorders in females, approximately affects 7 to 12% of women of reproductive age [1]. High androgen levels, ovulation disorder, and the presence of polycystic ovaries are considered diagnostic criteria for PCOS. Also, an increase in testosterone, luteinizing hormone (LH), and anti-Müllerian hormone (AMH) and a decrease in the secretion of follicle-stimulating hormone (FSH) contribute to the development of PCOS [2]. A wide range of reproductive abnormalities including menstrual disorders, infertility, hirsutism, and hyperandrogenism are represented in PCOS. Beyond hormonal disorders, obesity, insulin resistance, and chronic inflammation that increase the risk of metabolic syndrome, type 2 diabetes, and cardiovascular diseases are often associated with PCOS [3].

Recently, dietary interventions have been taken into consideration for the management of PCOS. Because up to 60% of PCOS women are overweight or obese, evidence-based international guidelines emphasize the importance of diet and recommend dietary and exercise interventions as the first line of management for this disorder [4]. To date, several diets including low-glycemic index diet [5], DASH diet [6], Mediterranean diet [7], low-carbohydrate diet [8], and ketogenic diet [9] have been proposed for the management of PCOS. However, there is a knowledge gap to suggest the best particular dietary intervention for improving PCOS health outcomes [4].

Intermittent fasting (IF) is a promising alternative, which has been shown to improve cardiometabolic status while adhering to weight loss goals [10]. IF is the practice of alternating between eating and fasting. IF is a general term for three different types of diets: alternate-day fasting (ADF), the 5:2 diet, and time-restricted feeding (TRF) [11]. Among the IF diets, the TRF diet is a lifestyle intervention that limited the duration of food intake to a fixed number of hours, without calorie counting or dietary recommendations [12]. Besides, past considerations recommend that TRE is attainable and accessible to upgrade adherence [13, 14]. IF diets could be beneficial in reducing body weight, improving insulin resistance, and reducing inflammation by affecting the circadian rhythm, intestinal microbial composition, and regulating metabolism [15]. Since disturbance in the circadian rhythm is related to insulin resistance, excess androgen production, increased levels of AMH, and apoptosis of granulosa cells, IF diets especially the TRF diet might alleviate PCOS by improving circadian rhythm [16–20]. Also, IF diets could ameliorate PCOS by decreasing insulin resistance through stimulation of AMP-activated protein kinase (AMPK) [21].

On the other hand, the microbiological hypothesis proposed that the microbial composition of the gut plays a crucial role in the pathogenesis of PCOS. Recent studies have demonstrated that dysbiosis of gut microbiota is related to sex hormone levels and ovarian morphological changes [22, 23]. Also, an imbalance in the gut microbial composition is associated with obesity, insulin resistance, and inflammation [24]. Probiotics could be used as a probable treatment for PCOS by changing gut microbiota, reducing insulin resistance, and improving inflammatory, antioxidant, and hormonal status [25]. Certain species of *Lactobacillus* and *Bifidobacterium* have been proposed as the most effective species for regulating sex hormones and metabolic parameters [26, 27]. Lactobacillus species contain beta-glucuronidase enzymes, allowing them to break down estrogens in the gut [28]. Moreover, *Lactobacillus* species resulted in the production of short-chain fatty acid metabolites (SCFAs) that reduced insulin resistance and inflammation and modulated androgen levels [29]. It has been shown that lactobacillus transplantation could partially reduce androgen production as well as the abnormalities in the estrous cycle and ovarian morphology caused by letrozole in PCOS-like rats induced with letrozole [30]. *Lactobacillus rhamnosus* supplementation enhanced the effectiveness of weight loss therapy for obese women, as demonstrated by Hulston et al. [29]. According to reports, *Limosilactobacillus reuteri* regulates host lipid metabolism, insulin sensitivity, inflammatory status, and immune response [31, 32]. The *Limosilactobacillus reuteri* was shown to improve glucose tolerance in rats with constant darkness-induced PCOS in a previous study [33].

Several studies investigating the synergistic effect of probiotic supplementation with a low-calorie diet have reported profitable effects of them to improve health status [34–37]. A recent study has demonstrated that the administration of probiotics in addition to a calorie-restricted (CR) diet resulted in significant weight loss [37]. Therefore, probiotics were introduced as an innovative strategy to increase the effectiveness of CR diets for weight control [38]. To the best of our knowledge, no clinical trial has investigated the effect of IF diet combination with probiotics supplementation in patients with PCOS. Therefore, the present study aims to investigate the effects of IF alone or in combination with probiotic supplementation compared to the CR diet on anthropometric measures, metabolic status, inflammation, and oxidative stress in women with PCOS.

## Subjects and methods

### Study design

The present placebo-controlled, parallel-arm, randomized, double-blind clinical trial examining the effects of IF diet alone or in combination with probiotic supplementation compared to the CR has been registered at the Iranian Registry of Clinical Trials (ID: IRCT20121110011421N5) on October 3, 2022. This trial will be performed at Arash Hospital, Tehran, Iran. Written informed consent will be obtained from participants before participation in the research project by researchers. We developed the study protocol based on the Standard Protocol Items: Recommendations for Interventional Trials (SPIRIT) 2013 checklist (Supplemental file 1). The timeline of the trial and study flow chart of enrolment, allocation, intervention, and assessment are presented in Table 1 and Fig. 1, respectively. A Standard Protocol Items: Recommendations for Interventional Trials (SPIRIT) diagram for the trial schedule is illustrated in Fig. 2. Any amendments to the present study protocol which have related to the safety and benefit of patients and the protocol deviations, unintentional alterations in study protocol that do not affect the subject’s rights, study’s risk or benefit, the integrity of data, and safety or welfare will require to be confirmed by Department of Clinical Nutrition and Medical Ethics Committee of Tehran University of Medical Sciences, Tehran, Iran, before the study conduction. Any alteration in the study protocol will be sent to the Trials journal (www.trialsjournal.biomedcentral.com).

**Table 1 Tab1:** Timeline of the trial

Explanation of the trial activities	Time (months)																	
	1	2	3	4	5	6	7	8	9	10	11	12	13	14	15	`16	17	18
Material preparation	*	*	*	*														
Recruitment					*	*	*	*	*									
Clinical assessments at baseline					*	*	*	*	*									
Nutritional assessments at baseline					*	*	*	*	*									
Biochemical assessments at baseline					*	*	*	*	*									
Intervention										*	*	*	*	*				
Clinical assessments after intervention										*	*	*	*	*				
Nutritional assessments after intervention										*	*	*	*	*				
Biochemical assessments after intervention										*	*	*	*	*				
Data analysis															*	*		
Writing the final report of the trial																	*	*
The expected time	*	*	*	*	*	*	*	*	*	*	*	*	*	*	*	*	*	*

**Fig. 1 Fig1:**
[figure not shown]
Summary of the patient flow diagram. TRF, time-restricted feeding; CR, calorie restricted

**Fig. 2 Fig2:**
[figure not shown]
SPIRIT diagram of the recommended content for the schedule of enrolment, interventions, and assessments

### Study setting

Subjects’ recruitment process will be advertised through the presence of patients at Arash hospital for treatment and diagnosis of diseases as well as through flyers distributed at women’s clinic centers in Tehran, affiliated with Tehran University of Medical Sciences, the province’s main center for treatment, prevention, research, and services. Participants will be selected from PCOS patients who are newly diagnosed by an expert gynecologist using Rotterdam criteria [39]. Candidates who are interested will be invited to the screening process.

### Study participants and enrollment

PCOS patients will be recruited from the clients of Arash Hospital by two independent researchers. An adept gynecologist with sufficient expertise in the diagnosis of PCOS will diagnose patients with PCOS based on the Rotterdam criteria. Patients who satisfy the following inclusion criteria will be eligible to participate in this research project.

### Inclusion criteria

The inclusion criteria are considered as follows: individuals aged between 18 and 40 years, subjects whose BMI ranged between 25 and 35 kg/m^2^ and who definitely eat breakfast, diagnosis of PCOS by a specialist based on the Rotterdam criteria for the first time (new cases) without medical treatment, and having or using a Smartphone.

### Non-entry criteria

Applicants will not be eligible if they are pregnant or breastfeeding or menopause; are night shift workers; are using antibiotics for at least 3 months before the intervention; have history of smoking, alcohol, and drug abuse; have inability to fast due to overnight medication; are consuming fermented products and foods containing probiotics; are being on a special or prescribed diet for various reasons; or have diabetes mellitus, hypertension, liver and kidney disorders, cancer, acute or chronic infectious diseases, type 1 and 2 diabetes, severe gastrointestinal diseases, Cushing’s disease, adrenal disease, acromegaly, gigantism, and an eating disorder.

### Exclusion criteria

Participants will be excluded if they had an antibiotic intake, allergic reaction to the supplement, getting infected with COVID-19, low adherence of patients to the intervention, or taking any medication affecting weight, appetite, hormonal status, carbohydrate, or lipid metabolism during the study.

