### Adherence to the intervention

All subjects will receive telephone calls per week and monthly meetings with a dietitian during the intervention to encourage adherence to the diet. We will send a daily reminder via instant messages that inform them when to stop eating and when they are allowed to eat. Furthermore, periodic meetings (once every 30 days) should be promoted for participants to share their experiences and receive support from physicians. Moreover, all people are given detailed written and oral instructions for each meal plan, and as mentioned, there is no difference between people participating in the fasting diet and the low-calorie diet. Monitoring of food programs is done through the daily interaction of the researcher and the participant in the project through phone conversations. If they do not attend more than two consecutive phone sessions or consume 3 inappropriate meals or fail to follow the diet instructions 3 times a week for more than 2 consecutive weeks is considered non-compliant patients [44, 45]. A 3-day 24-h dietary recall will be taken from the participants every 2 weeks to confirm compliance.

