### Statistical analysis

All analyses will be performed according to the Intention to Treat Analysis (ITT) method. Therefore, all participants who entered the study (regardless of whether they completed the 8-week study period) are included in the analysis. Missing data will be checked by multiple imputations. Statistical analysis will be conducted using the SPSS software (Version 24, SPSS Inc., and Chicago, IL, USA). The scatter diagram, histogram, and Kolmogorov–Smirnov test will be applied to examine the normality of the data. Normally distributed variables will be reported as the mean and standard deviation, while the median and interquartile range (IQR) will be used for reporting non-normally distributed variables. Moreover, we will use the chi-square test and Fisher’s exact test to compare categorical variables. Also, the independent sample *t*-test and Mann–Whitney U test will be applied to compare continuous variables between-group, whereas we will use paired sample *t*-test and Wilcoxon rank-sum test for within-group comparisons. To compare the differences in primary and secondary outcomes between the two study groups at the end of the trial and adjust the final findings for potential confounders, we will apply the mixed linear effect model. To correct for multiple comparisons and reduce alpha error, *q* values will be used using the Benjamin-Hochberg method. Based on this, significance was defined in *P* values less than 0.05 and *q* values less than 0.1. Cohen’s *d* will be calculated based on the mean and standard deviation. The effect sizes 0.20, 0.50, and 0.80, respectively for low, medium, and high therapeutic effects of the dietary intervention will be determined. No subgroup analyses are planned. However, no interim analyses are planned for this trial.

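### Exclusions after randomisation, including for low adherence, are not reconciled with the stated intention-to-treat analysis

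*Protocol article*

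**What the plan says.** The protocol article has two separate lists. Its Non-entry criteria section covers ineligibility at baseline. Its Exclusion criteria section covers later events: "Participants will be excluded if they had an antibiotic intake, allergic reaction to the supplement, getting infected with COVID-19, low adherence of patients". That list closes with interfering medication, worded as "taking any medication affecting weight, appetite, hormonal status, carbohydrate, or lipid metabolism during the study".

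The Adherence to the intervention section defines non-compliance by behaviour on treatment. One trigger is "If they do not attend more than two consecutive phone sessions"; another is that participants "fail to follow the diet instructions 3 times a week for more than 2 consecutive weeks is considered non-compliant patients". It gives two contact frequencies: "All subjects will receive telephone calls per week" and "Monitoring of food programs is done through the daily interaction of the researcher and the participant", the latter also by phone.

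The Statistical analysis section adopts ITT, under which "all participants who entered the study (regardless of whether they completed the 8-week study period) are included in the analysis", and handles missing data by multiple imputation. The Outcomes section places all outcome measurement before and after the intervention. The Randomization and blinding section says that diet is not blinded.

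**The concern.** A participant who meets an exclusion criterion in, say, week 4 is covered by two instructions. One section excludes her and another includes her in the analysis. The article does not say whether exclusion ends the diet or supplement, ends follow-up, or removes her from the analysis.

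The reasons matter as much as the number. Low adherence is likely to be related to weight change. It also means different things under an ad libitum eating window and under a menu cut by 25% of energy needs, so the proportion excluded may differ by arm. Compliance is monitored by a researcher over the phone, and diet is not masked. Reactions to the supplement could also differ between probiotic and placebo. If these participants' outcomes are lost or left out, the result moves towards an effect among adherers while carrying the ITT label.

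**Working it through.** **1. Are the exclusions after randomisation?** Yes. Baseline ineligibility has its own list, the medication criterion refers to use during the study, and non-compliance is judged on calls, meals and diet behaviour under treatment.

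**2. What could exclusion mean?**

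| Reading | Consequence |
|---|---|
| Removed from the analysis | Contradicts the ITT statement; nothing is imputed |
| Follow-up stops, kept in the set | ITT set kept in name; week-8 values are imputed |
| Intervention stops, outcomes still collected | No conflict with ITT |

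The article does not choose. The Data management and monitoring section speaks of excluding participants from the trial after adverse events, which favours the first two readings. Its sentence on outcome data for those who discontinue or deviate is unclear. The Consent section only asks permission to use data after withdrawal.

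**3. Planned reserve (Sample size calculation section).** Stated: 25 per group, 5% drop-out, 30 per group.
- 25/0.95 = 26.3, so 27 would cover 5%. Going from 25 to 30 covers 1 - 25/30 = 16.7% loss.
- The 25 is not reproduced by the printed two-sided formula: (1.960 + 0.842)² × (3.87² + 3.04²)/2.5² = 7.849 × 24.219/6.25 = 30.41, so 31. A one-sided test gives 23.96, so 24 (25 by the t distribution). That is a separate matter, but it means that 30 holds no reserve on the two-sided inputs.
- Two-sided power for 2.5 kg (normal approximation, SD 3.48) if excluded participants contribute no outcome:

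| Loss | n per group | Power |
|---|---|---|
| 0% | 30 | 79.5% |
| 5% | 28.5 | 77.4% |
| 10% | 27 | 75.2% |
| 20% | 24 | 70.2% |
| 30% | 21 | 64.4% |

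**4. Bias.** Let m be the mean loss among retained participants in an arm, p the proportion excluded, and g how much less the excluded lose. The all-randomised mean is m - p·g. Dropping the excluded, or imputing them at the retained mean of their own arm, gives m. With the difference taken as TRF minus CR,

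bias = p_TRF·g_TRF - p_CR·g_CR.

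The document gives neither p nor g. The values below are assumptions, with excluded participants losing 0 kg (so g = m):

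| m, TRF / CR (kg) | p, TRF / CR | Shown | All randomised | Bias |
|---|---|---|---|---|
| 4.0 / 1.5 | 5% / 5% | 2.5 | 2.38 | +0.12 |
| 4.0 / 1.5 | 10% / 10% | 2.5 | 2.25 | +0.25 |
| 4.0 / 1.5 | 20% / 20% | 2.5 | 2.00 | +0.50 |
| 4.0 / 1.5 | 30% / 10% | 2.5 | 1.45 | +1.05 |
| 4.0 / 1.5 | 10% / 30% | 2.5 | 2.55 | -0.05 |
| 2.5 / 2.5 | 30% / 10% | 0 | -0.5 | +0.5 |
| 3.0 / 3.0 | 10% / 30% | 0 | +0.6 | -0.6 |

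For example, row four is 0.30 × 4.0 - 0.10 × 1.5 = 1.20 - 0.15 = 1.05 kg. The sign changes with the arm that loses more people, and equal exclusion rates do not guarantee zero bias.

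**5. Phone trigger.** More than two consecutive misses means at least three: three weeks of weekly calls, or three days of daily contact, a seven-fold difference.

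**The case against.** The strongest reply is that the ITT sentence is explicit and covers non-completers. Exclusion may mean only that the intervention stops, with outcomes still collected, and then nothing conflicts. That reading is possible, but no section states it, and the wording on excluding people from the trial points the other way. Reconciliation is still needed.

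Other parts of the reply stand, and they limit what can be said:

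- A reader might infer that non-adherers' outcomes will be replaced by values imputed from adherers. The article does not say so. It states neither that excluded participants lack a week-8 value nor what the imputation model is. The model is properly left to a fuller document, and the fortnightly dietary recalls and repeated activity records could inform it. This outcome and removal from the analysis are also alternatives, not one combined fault.
- A reader might want one bias range. Multiplying the difference in exclusion rates by a single gap, for instance 0.15 × 2 = 0.3 kg up to 0.20 × 4 = 0.8 kg, holds only if the gap is the same in both arms. A gap due to non-adherence also need not apply to people excluded for antibiotics, COVID-19, allergy or new medication.
- A reader might infer that the 5% drop-out figure leaves no room for exclusions. Against the stated 25, enrolling 30 allows 16.7%.
- The phone-session ambiguity is minor. The article labels these participants non-compliant; that this is the low adherence leading to exclusion is a reasonable inference, not a statement.

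**Conclusion.** The point holds in conditional form. It is well supported that participants can be excluded after randomisation, for low adherence among other reasons, and that this is not reconciled with an analysis of everyone who entered. The consequence depends on what exclusion means: either the analysis is not ITT, or part of the ITT result rests on imputed values with no interim weight to support them. That the exclusions are informative and differ by arm is plausible, given unblinded diets with different demands, but is not shown.

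The size cannot be fixed from the document. The scenarios above show biases from -0.6 to +1.05 kg, with some close to zero, and they rest on assumed rates and gaps. Because the point decides who counts in the primary analysis, it should be settled before the data are analysed.

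**What to change.** In the Exclusion criteria and Statistical analysis sections, state that:

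- a participant with a listed event is recorded as a protocol deviation and is still invited to the scheduled week-8 outcome visit, whether or not she continues the diet or supplement;
- she is analysed in the arm to which she was randomised, using observed data;
- imputation is used only for values that are truly missing;
- the listed events and the non-compliance definition serve only to define a labelled per-protocol sensitivity analysis;
- exclusions are reported by arm and reason.

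In the Adherence to the intervention section, say whether a phone session is the weekly call or the daily contact.

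The cost is wording plus a visit that is already scheduled. No rule on stopping treatment needs to change. Recruitment was expected to be almost finished on 23 September 2023, so the change may come too late to obtain week-8 data from some participants already excluded; for them, use any week-8 data that were observed. The downside is that the ITT effect may look smaller than an adherers-only effect.
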